### Blinding

2.4

The participants and assessors will be blinded, not be aware of the group allocation. Statistical analysis will also be conducted by data analysts without awareness of the group allocation. Only clinicians applying rTMS intervention will not be blinded, as they will apply rTMS over different stimulation sites based on the protocols. Blinding will be continued until the end of the study, including data analysis.

In addition, all participants will receive inpatient conventional rehabilitation therapy, consisting of occupational and physical therapy for 30 min each, twice daily, for 2 weeks, as well as the routine pharmacotherapy based on the guidelines for management of stroke patients (47–49).

During the intervention, participants are allowed to withdraw based on the following criteria: (1) those willing to withdraw, (2) loss to follow-up, (3) occurrence of adverse events, following withdrawal requests from participants, (4) other reasons deemed unsuitable for the progress of the study by the researchers.

## Data collection

3

### Brain imaging and cortical excitability

3.1

Brain imaging data, comprising rs-fMRI, DTI, and T1-weighted structural images, will be obtained using 3-T scanners (Philips Ingenia CX, Philips Elition, Siemens Magnetom Trio, Siemens Magnetom Vida). The rs-fMRI will be employed to extract brain networks through functional connectivity analysis. Alterations in brain network properties resulting from the intervention will be investigated by analyzing connectivity strength, employing graph theory, and conducting comprehensive assessments of both global and local networks, as well as intra- and inter-hemispheric networks (50). During the resting-state scan, participants will be directed to close their eyes and maintain stillness. Each session will involve the collection of 180 whole-brain images, utilizing the following metrics: 75 axial slices, slice thickness = 2 mm, no gap, matrix size = 112 × 112 or 124 × 124, and repetition time = 2000 ms. DTI will be utilized to extract the integrity of major neural pathways and structural networks through fiber tractography (51). It will also be used to investigate changes in the characteristics of integrity and networks resulting from the intervention (52). Each session will acquire more than 30 diffusion-weighted images with b = 1,000 s/mm2, ensuring a minimum of 75 axial slices, slice thickness = 2 mm, no gap, and matrix size = 112 × 112 or 128 × 128. Fractional anisotropy values (FA) of posterior limb of internal capsule (PLIC), and reconstructed corticospinal and corticobulbar tract will be obtained (53, 54). T1-weighted structural images will be used to ascertain the individual target positions of the ventral PM. These images will be acquired with a resolution and slice thickness of 1 mm or less to accurately guide the position of the TMS coil.

The cortical excitability of each participant will be measured, using the TMS-induced MEPs. TMS-induced MEPs will be assessed by single magnetic stimulations at 120% of the rMT over the M1 using a 70-mm figure-of-eight coil. During the experiments, participants will sit comfortably in an armchair with their eyes open. A Synergy electromyography/evoked potentials system (Medelec Co. Ltd., Kingswood, Bristol, United Kingdom) will be used to record and monitor the activity of the contralateral FDI muscle following stimulating over the M1 using single-pulse TMS. TMS will be applied using a BiStim^2^ stimulator (Magstim Co. Ltd., [name], Wales, United Kingdom) equipped with a 70-mm figure-of-eight coil. The coil would be held tangentially to the scalp, with the handle pointing backward and laterally at 45° from the mid-sagittal line. Using TMS, the optimum position (“the hot spot”) will be defined as the site where TMS-induced MEPs of maximum peak-to-peak amplitude in the contralateral FDI muscle. We will define the rMT as stimulus percentage of maximal stimulator output (MSO) that elicits a minimum peak-to-peak amplitude of MEP over 50uV in at least 5 out of 10 trials (5). This rMT data will be used for determining the intensity of the rTMS intervention in this study. Including the aforementioned rMT, amplitude and latency of MEP will be recorded as TMS-induced MEPs data. To measure the amplitude and latency, the intensity of the TMS stimulation will be set at 120% of the measured rMT. The stimulation will be repeated 10 times, with intervals of 5 s or more. The average peak-to-peak amplitude and latency of the top 5 responses will be measured and recorded (55). The latency will be the time between the onset of the TMS stimuli and the onset action potential (56). In addition, medications known to have potential effects on MT or MEP and the risk of seizures associated with rTMS will also be documented (15, 57).

### Functional assessment

3.2

Functional assessments will be conducted at T0, T1, T2, and T3 periods in each participating hospital. To maintain the data quality and inter-rater reliability, the assessors will be trained before the start of the study and uniform manuals will be shared with the assessors and research investigators. In this study, all functional assessment tools selected are widely used for stroke patients and have been frequently employed in previous studies using rTMS (22, 23). Additionally, their reliability and validity have been proven. For motor function, FMA will be used. FMA measures the movement, reflexes, coordination, and speed of limbs (58, 59). The total, upper extremity (UL), and lower extremity (LL) score of FMA will be assessed separately. For hand function assessments, the following tests will be used: the Box and Block Test, reflecting clinical manual dexterity (60, 61); the Action Research Arm Test (ARAT), measuring gross motor skills, grasp., grip, and pinch (62); the Jebsen-Taylor Hand Function Test, assessing the fine motor function of the hand used in daily activities (63, 64); and the Hand Grip Strength Test (65). The Functional Ambulation Category (FAC) will be used to assess ambulatory function, categorizing patients by their level of dependence in walking (66).

### Outcomes

3.3

The primary outcome of this study is difference of FMA-UL from baseline (T0) to post-intervention (T2). The secondary outcomes of this study are as follows:

Differences of FMA-total, FMA-UL, FMA-LL, Box and block test, FAC, ARAT, Jebsen-Taylor hand function test, hand grip strength test from baseline (T0) to during-intervention (T1).Differences of FMA-total, FMA-LL, Box and block test, FAC, ARAT, Jebsen-Taylor hand function test, and hand grip strength test, FA of PLIC, FA of reconstructed corticospinal and corticobulbar tract, global and local connectivity obtained from rs-fMRI from baseline (T0) to post-intervention (T2).Differences of FMA-total, FMA-UL, FMA-LL, Box and block test, FAC, ARAT, Jebsen-Taylor hand function test, and hand grip strength test, FA of PLIC, FA of reconstructed corticospinal and corticobulbar tract, global and local connectivity obtained from rs-fMRI from baseline (T0) to follow-up (T3).

### Sample size, recruitment

3.4

Based on the primary outcome of this study and previous literature, we have established the study’s power (1-β) at 80% and a significance level (α) of 5%. The clinically significant effect size (δ) has been designated as 7.25, with an expected standard deviation (σ) of 7.70 (67, 68). Sample size calculation was conducted using Lehr’s formula, with an expected follow-up rate of 90% (68, 69). Finally, the calculated sample size was 120, with each subgroup consisting of 40 participants.

Recruitment of the study participants will be conducted by each participating hospital.

Every research investigator will recruit participants from each hospital who are eligible to participate in the study. Participants will be informed about the current treatment guidelines regarding upper extremity dysfunction in stroke patients, as well as the potential and adverse effects of this study.

### Statistical methods

3.5

Demographic and clinical characteristics were reported in terms of frequencies and percentages for categorical variables, while means and standard deviations (SD) were utilized for numerical variables. To compare baseline characteristics of the intervention and control group, an independent t-test and the Wilcoxon Signed-rank test will be used for normally distributed and non-normally distributed variables, respectively. The normality of each variable will be examined using the Shapiro–Wilk test.

All participants undergoing intervention in this study will be included in the intention-to-treat (ITT) set. Safety analyses will be conducted based on the ITT set. Participants who completed all of the evaluation regarding the study protocol will be classified as per-protocol (PP) set. The efficacy analyses will be conducted based on the ITT set. For missing values, data will be analyzed using the Last Observation Carried Forward (LOCF) method. Efficacy analyses well be conducted on the primary and secondary outcomes. For outcome variables, the normality will be examined using the Shapiro–Wilk test. If variables demonstrate normal distribution, a repeated measures analysis of variance (RM-ANOVA) will be used to evaluate the effect of time and groups, including the interaction. If non-normality is found, the Friedman test will be used to determine the differences between the groups. During the analyses, baseline characteristics will be used as covariates for adjustment. In addition, independent t-test or Wilcoxon Signed-rank test will be used to compare parameters between the intervention group and the control group in each condition. Statistical significance will be set at a *p*-value <0.05 for all the analyses.

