### Eligibility criteria

2.2

The inclusion criteria for this study are as follows: (1) hemiplegic stroke (ischemic or hemorrhagic stroke with corresponding lesion determined by MRI or computed tomography scan) patients in the subacute phase (7 days to 3 months from the onset) who are currently hospitalized, (2) Fugl-Meyer Assessment (FMA) score of the upper extremity ≤42, (3) adequate language and cognitive function to perform at least a 1-step obey-command, (4) pre-stroke functional level of modified Rankin Scale (mRS) ≤1, (5) aged ≥19 years old, and (6) patients willing to sign the informed consent. The exclusion criteria are as follows: (1) patients with transient ischemic attack, defined as a rapid-onset focal neurological deficit lasting less than 24 h (42) (2) those with contraindications to rTMS, such as epilepsy, implanted metal objects in the head, or a history of craniotomy, (3) those with progressive of hemodynamically unstable medical conditions, (4) those with coexisting neurological conditions, such as spinal cord injury or Parkinson’s disease, (5) those with major psychiatric disorders, such as major depression, schizophrenia, or dementia, (6) those having contraindications to conduct an MRI study, (7) those who are pregnant or lactating, and (8) patients who have refused to participate in this study.

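### LOCF is the only missing-data rule for efficacy in patients still recovering, so the arm difference can be biased in a direction set by the dropout pattern

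*Protocol article*

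**What the plan says.** All of this is in the protocol article.

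- **Missing data** (Statistical methods): "For missing values, data will be analyzed using the Last Observation Carried Forward (LOCF) method". The sentence is not limited to any outcome or visit, and no other approach is named.
- **Analysis set** (Statistical methods): "The efficacy analyses will be conducted based on the ITT set". That set is everyone who undergoes intervention. A per-protocol set is defined, but no analysis is assigned to it.
- **Primary outcome** (Outcomes): "The primary outcome of this study is difference of FMA-UL from baseline (T0) to post-intervention (T2"). The other function scores are compared as changes from T0 to T1, T2 and T3, and the imaging measures as changes from T0 to T2 and T3.
- **Population** (Eligibility criteria): "patients in the subacute phase (7 days to 3 months from the onset) who are currently hospitalized". The Intervention section adds conventional rehabilitation twice a day for all participants during the two treatment weeks.
- **Visits** (Table 1): function is scored at T0, T1 (after one week), T2 (end of treatment) and T3 (two months later). Scans are taken at T0, T2 and T3 only.
- **Loss** (Sample size, recruitment): the calculation was made "with an expected follow-up rate of 90" percent, with no visit and no arm specified.
- **Withdrawal** (Intervention): the listed grounds include adverse events and "other reasons deemed unsuitable for the progress of the study by the researchers".

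**The concern.** LOCF assumes that a participant's score stays where it was last seen. This trial expects the opposite: patients are early after stroke, treated daily, and judged on how far they move. The rule acts differently by visit:

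- A participant last scored at T0 enters the primary outcome with a change of exactly zero.
- A participant last scored at T1 is credited with only the first week's change.
- A missing T2 scan is filled from T0, because there is no T1 scan, so it also becomes zero change.
- A missing T3 value is frozen at its T2 level, as if nothing happened in the two months between.

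The filled values then enter the time-by-group analysis as if observed. At stake is the size of the primary arm difference, and for T3 and imaging a larger share of the expected change. The protocol states this rule as its choice, so it is not a detail left open for a later analysis plan.

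**Working it through.** **Inputs from the article.** Sample size section: "The clinically significant effect size (δ) has been designated as 7.25, with an expected standard deviation (σ) of 7.70"; "power (1-β) at 80% and a significance level (α) of 5" percent; 90% follow-up. Allocation section: 1:1 within each condition of 40.

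**Assumptions not in the article.** Control-arm gain g from T0 to T2 of 3, 6 or 9 points; all loss falls before T2; the split of loss by arm; the share f of the T0-T2 change already present in the carried value (f = 0 for T0 carried, f = 0.5 for T1 carried with half the gain reached); loss unrelated to outcome within arm.

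**The plan's own figure.** Lehr: 16 / (7.25/7.70)² = 18.05 per arm. 18.05 / 0.90 = 20.05, so 20 per arm, 40 per condition, 120 in all. The stated figure reproduces.

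**Expected difference under LOCF.** With loss p_I (intervention) and p_C (control):

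D = (g + 7.25)[1 − p_I(1 − f)] − g[1 − p_C(1 − f)]

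| Loss I / C | f | D | g = 3 | g = 6 | g = 9 |
|---|---|---|---|---|---|
| 10% / 10% | 0 | 0.90 × 7.25 | 6.53 | 6.53 | 6.53 |
| 10% / 10% | 0.5 | 0.95 × 7.25 | 6.89 | 6.89 | 6.89 |
| 15% / 5% | 0 | 6.16 − 0.10g | 5.86 | 5.56 | 5.26 |
| 15% / 5% | 0.5 | 6.71 − 0.05g | 6.56 | 6.41 | 6.26 |
| 5% / 15% | 0 | 6.89 + 0.10g | 7.19 | 7.49 | 7.79 |
| 5% / 15% | 0.5 | 7.07 + 0.05g | 7.22 | 7.37 | 7.52 |

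Relative to 7.25, equal loss costs 10% (f = 0) or 5% (f = 0.5). With T0 carried, the 15/5 split costs 19% to 27%, and the 5/15 split moves the difference by −1% to +7%.

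**No true effect.** Replacing 7.25 by 0 and taking f = 0, equal loss gives D = 0. A 15/5 split gives D = −0.10g, that is −0.3 to −0.9 points, against the intervention. The 5/15 split gives the same size in its favour.

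**Power in one condition.** Two-sided t-test at 5%, 20 per arm, SD 7.70 taken as the SD of change, independent normal increments, 40,000 simulated trials, exactly two lost per arm:

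| Analysis | g = 3 | g = 6 | g = 9 |
|---|---|---|---|
| LOCF, T0 carried | 76% | 73% | 70% |
| LOCF, half the gain carried | 80% | 80% | 79% |

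The right comparator is the t-test on the 18 completers per arm that the plan allows for: 78.4%. (The normal approximation gives 80.6%, which is where the stated 80% comes from.) So LOCF loses about 2 to 8 points if T0 is carried and nothing if half the gain is carried.

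**Pooled conditions.** At 60 per arm, power is above 99% with full data. It is still about 99% under LOCF with 10% lost per arm and T0 carried.

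**The case against.** The strongest defence is that the effect is small where it matters most. The primary endpoint comes after two weeks in patients recruited as inpatients, with a score at one week. Early loss may be well under 10%, since the article does not tie its 90% to T2, and a dropout may well have a T1 score to carry. That stands: T0 carried is the unfavourable end of the range, and equal loss costs 5% to 10% of the effect.

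Four stronger readings are tempting, and the article does not support them.

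- **A reader might infer that LOCF cuts power below the planned 80%.** It does so only if T0 values are carried or the intervention arm loses more. Against 18 completers, carrying half the gain costs nothing, and with pooled conditions the loss is immaterial.
- **A reader might infer from the withdrawal criteria that loss will be unequal.** The same criteria apply to both arms, both receive active stimulation, and participants are blinded. No rate by arm is given. Unequal loss is possible but not documented, and it could fall on either arm.
- **A reader might infer that treating filled values as observed makes the test clearly anti-conservative.** With no true effect and T0 carried, simulated type I error was 3.5% to 4.8% with two lost in each arm and about 5% with three against one. When each participant is lost at random with probability 15% or 5%, it was between about 5% and 7% for control gains up to 10 points. Material inflation needs a more extreme split (up to 13% at 20% against 0%).
- **A reader might infer that assessment ends when stimulation stops.** The article does not say so, and a condensed article's silence is not a fault.

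None of this supports LOCF as the sole rule. Its bias depends on a dropout pattern unknown in advance. The power it appears to retain over a completers analysis comes partly from counting filled-in values as data.

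**Conclusion.** The concern holds in a limited form. LOCF is fixed as the only missing-data rule for efficacy in patients whose scores are expected to change, so the T0-T2 and T0-T3 arm differences are open to bias if a true effect exists or dropout differs by arm. The direction is not fixed: equal loss, or heavier loss in the intervention arm, shrinks a true benefit, while heavier loss in the control arm can enlarge it. At the planned 10% loss, equal in both arms, the primary difference shrinks by 5% to 10%. The assumed 15/5 and 5/15 splits with T0 carried span 5.3 to 7.8 points around the planned 7.25. These figures rest on assumed timing, split and control gain. T3 and imaging outcomes are more exposed than the primary outcome, because the carried value is older or is the baseline itself. Severity: should be fixed. The case rests on bias; power is a secondary and conditional matter.

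**What to change.** Replace LOCF as the primary rule with a likelihood-based mixed model for repeated measures using every observed FMA-UL score. Include arm by visit, baseline FMA-UL, and condition when conditions are pooled, with the T2 arm contrast as the primary result. Multiple imputation would serve equally well. Both rest on missingness at random, so add one sensitivity analysis under missingness not at random, for example a delta adjustment. LOCF may stay beside it as a sensitivity analysis, but should not decide the result. Apply the same principle to the T3 and imaging outcomes.

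The change should be made before unblinding. It costs a revised paragraph in Statistical methods and slightly more programming. It needs no extra participants or visits, and the sample size remains 120.

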### Study setting

2.1

This is a prospective, single-blind with blind observer, parallel-group design, multi-center, randomized controlled clinical trial. This study will recruit 120 patients with stroke in the subacute phase who are suffering from the upper extremity motor impairment, from five different hospitals in Korea. Participating hospitals are Samsung Medical Center, Seoul; Seoul National University Hospital, Seoul; Bucheon St. Mary’s Hospital, The Catholic University of Korea, Seoul; St. Vincent’s Hospital, The Catholic University of Korea, Seoul; Yongin Severance Hospital, Yongin.

The participants will be allocated into three different study conditions according to their functional reserve, as follows: Study condition (1) participants with preserved ipsilesional CST, confirmed by response of TMS-induced MEPs, Study condition (2) participants with no response of TMS-induced MEPs, but with preserved ipsilesional PM cortex and ipsilesional CST confirmed by DTI, and Study condition (3) participants with no preservation of ipsilesional CST. After the allocation, participants will be randomly assigned to the intervention-group or control-group of each study condition through randomization. The participants of the intervention-group in the three study conditions will receive different protocols of rTMS intervention: Study condition (1) high-frequency rTMS on ipsilesional M1, Study condition (2) high-frequency rTMS on ipsilesional ventral PM, and Study condition (3) high-frequency rTMS on contralesional M1. The participants of the control-group in all three study conditions will receive the same rTMS protocol: low-frequency rTMS on contralesional M1. A schematic diagram is shown in Figure 1.

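### A Shapiro–Wilk test on the outcome variables, not on model residuals, chooses the efficacy analysis, so the primary analysis depends on the data and the gate checks the wrong assumption

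*Protocol article*

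**What the plan says.** Section 3.5 (Statistical methods) of the protocol article sets a two-step rule for efficacy. Step one: "For outcome variables, the normality will be examined using the Shapiro–Wilk test". Step two has two branches: "If variables demonstrate normal distribution, a repeated measures analysis of variance (RM-ANOVA) will be used to evaluate the effect of time and groups", with their interaction; and "If non-normality is found, the Friedman test will be used to determine the differences between the groups". The next sentence says baseline characteristics will serve as covariates. A further comparison follows: "independent t-test or Wilcoxon Signed-rank test will be used to compare parameters between the intervention group and the control group in each condition".

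Residuals and model errors are not mentioned. Nor does the section say whether the test is run on visit scores or change scores, pooled or within arm or condition, or how several results are combined.

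Other relevant facts in the article:
- Section 2.1: "The participants will be allocated into three different study conditions according to their functional reserve".
- Section 3.2: function is measured at four visits, T0 to T3.
- Section 3.3: the primary outcome is the FMA-UL difference from T0 to T2.

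**The concern.** RM-ANOVA assumes that the errors are roughly normal once group and visit are accounted for. It does not assume that the outcome variable follows a single normal curve. In a trial that sorts patients by functional reserve, pooled FMA-UL scores can be a mixture of severities and fail Shapiro–Wilk while the errors are normal. Repeating the test over visits adds false alarms.

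Three things are at stake. The analysis of the primary endpoint is picked by the trial's own data. If the gate fires, the analysis moves from a model with a group-by-time interaction and covariates to a test with neither, although the same section promises adjustment. And different outcomes may end up analysed by different methods.

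**Working it through.** **Design figures reproduced.** Section 3.4 gives δ = 7.25, σ = 7.70, α = 5%, power 80%, follow-up 90%, and names Lehr's formula.
- n per arm = 16 × (7.70/7.25)² = 18.05.
- Allowing for dropout: 18.05/0.9 = 20.05, taken as 20.
- 20 × 2 arms × 3 conditions = 120, as stated. The gate therefore acts on 20 per arm and 40 per condition, or 120 if pooled.

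The article gives no figure for the gate itself, so its behaviour was simulated (Shapiro–Wilk at 0.05, at least 1,500 replicates per setting). Errors were exactly normal, so every rejection discards a model whose normality assumption holds. Condition means, visit SDs and visit correlations are assumptions.

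**1. Residuals, the quantity the model concerns.** After removing condition and arm means, rejection is 4–6% whatever the severity mix.

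**2. One test on the T0–T2 change.** With SD 7.7 and an arm effect of 7.25, pooled over 120 patients:
- assumed mean changes 12/8/4: 3.8%
- 18/10/3: 3.9%
- 25/12/3: 10.1%

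Within one condition the rate is about 5%.

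**3. Visit scores within one condition (n = 40), any of four visits.** Independent tests would give 1 − 0.95⁴ = 18.5%. Simulation gives 14–19% for correlations from 0 to 0.9. Splitting by arm gives 1 − 0.95⁸ = 33.7% if independent, and 26–34% simulated.

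**4. Visit scores pooled over conditions (n = 120), any of four visits, correlation 0.8.**

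| Assumed condition means | Visit SD 5 | Visit SD 7.7 | Visit SD 12.2 |
|---|---|---|---|
| equal | 15.4% | 15.6% | about 16% |
| 26/20/14 | 17.0% | 13.8% | not run |
| 30/18/10 | 86.7% | 28.1% | 14% |
| 34/18/8 | 100% | 64.8% | 19% |
| 34/12/6 | 100% | 98.9% | 42% |

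Repeat runs at SD 12.2 span 12–46%.

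The last column matters because section 3.4 bases σ = 7.70 on the primary outcome, which is a change. Change SD = visit SD × √(2(1 − 0.8)) = 0.632 × visit SD. Visit SDs of 5 and 7.7 therefore imply change SDs of only 3.2 and 4.9. A change SD of 7.7 needs a visit SD of 7.7/0.632 = 12.2.

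**5. Does the gate protect anything?** The two-sample t-test was checked with exponential, lognormal and t₅ errors. Its type I error is 4.2–4.7% at 20 per arm and 4.7–5.4% at 60 per arm. In the same settings Shapiro–Wilk rejects in 99–100% of trials for the two skewed distributions, and in 30% (n = 40) and 62% (n = 120) for t₅. For the comparison of mean change between arms, the gate guards against little.

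**The case against.** The strongest reply is that the article's outcome variables are differences. Section 3.3 defines the primary outcome as a T0–T2 change, and a single test on that change misfires at close to its nominal 5%. The sample size is built per condition and arms are compared within conditions; if normality is checked there too, the severity mixture disappears. Testing within each arm and visit comes near the assumption RM-ANOVA does make. All of this stands as to frequency. It does not settle which reading is meant: RM-ANOVA with a time factor needs visit scores, and only the added t-test or Wilcoxon comparison is confined to a condition.

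A reader might infer that a sound model would often be discarded because of the severity mix. The document does not support that. Pooling, visit scores and an any-visit trigger are one reading among several. A spread of 26/20/14 gives rates close to those for equal means. The highest rates need well-separated means, mostly with visit SDs smaller than the stated σ implies. Nor can exactly normal errors hold at the extremes: with means 34/12/6 and SD 7.7, about 22% of the lowest condition falls below zero and about 15% of the highest exceeds the entry limit of 42. With bounded scores the errors are non-normal too.

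It is also fair to say that part of the harm comes from naming Friedman as the fallback, which is a separate defect. A valid between-arm rank test behind the gate would still leave the choice of analysis to a pre-test. The point that visits would be analysed by different methods fails, because RM-ANOVA and Friedman each use all visits together.

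Finally, an unseen analysis plan could say how the gate is applied. The gate itself is fixed in the article.

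**Conclusion.** The point holds as a defect of specification. Section 3.5 lets a normality test on the outcome variables choose the efficacy analysis. That test does not address the model's assumption about errors, and the switch removes the interaction and the covariate adjustment promised in the same section.

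The size is conditional. With normal errors, the chance of discarding a sound model is:
- about 5% for one test on the T0–T2 change (4–10% over the scenarios tried);
- about 15% for equal means, or within one condition, if any of four visits triggers the switch;
- about 12% to 100% for visit scores pooled over conditions with assumed severity differences.

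The article gives no condition means, visit SDs or correlations, so the last range shows what the wording permits and is not a forecast. The case for change does not depend on the upper figures. It should be corrected before the data are analysed.

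**What to change.** In section 3.5, delete the Shapiro–Wilk gate for outcome variables and replace it with one prespecified primary analysis of FMA-UL. An example is a linear model for the T0–T2 change with arm, condition and baseline FMA-UL. Examine residuals as a diagnostic only, with no power to change the primary analysis. Always report one prespecified between-arm sensitivity analysis that does not rely on normality, such as a re-randomisation test of the adjusted arm effect stratified by condition.

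The cost is two rewritten sentences and one additional analysis. Data collection and sample size are unchanged.

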### Allocation

2.3

The 120 eligible participants will be allocated into three study conditions based on the functional reserve of each participant, measured by the results of the brain MRI, TMS-induced MEPs, and DTI evaluations. Each condition will consist of 40 patients and they will be randomly allocated into the intervention-group and control-group in a 1:1 ratio. The allocation will be performed by the one researcher of each participating hospital, who will be responsible for the randomization, will not have contact with the participant, and will not be involved in data collection or analysis. The randomization will be done by using a randomization table generated by the www.randomization.com. The randomization sequence will be concealed and only the research principal investigator (PI) will have access authority.

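### No analysis is designated primary, and the RM-ANOVA named for efficacy is not tied to the T0-to-T2 FMA-UL change or to study condition

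*Protocol article*

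**What the plan says.** The Outcomes section fixes one primary outcome: "The primary outcome of this study is difference of FMA-UL from baseline (T0) to post-intervention (T2". The T0-to-T1 and T0-to-T3 changes in the same score are secondary outcomes. Under Functional assessment, "Functional assessments will be conducted at T0, T1, T2, and T3 periods in each participating hospital".

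Statistical methods applies one scheme to primary and secondary outcomes alike. If a Shapiro-Wilk test supports normality, "a repeated measures analysis of variance (RM-ANOVA) will be used to evaluate the effect of time and groups, including the interaction". If not, the Friedman test is to establish group differences. On adjustment it says "During the analyses, baseline characteristics will be used as covariates for adjustment", without listing the characteristics. A t-test or Wilcoxon test is then added to "compare parameters between the intervention group and the control group in each condition". The section does not say which parameters, or at which visits.

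On design, Study setting says that "participants will be randomly assigned to the intervention-group or control-group of each study condition through randomization", and Allocation says: "Each condition will consist of 40 patients and they will be randomly allocated into the intervention-group and control-group in a 1:1 ratio". The intervention arms of the three conditions receive different active protocols.

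**The concern.** The primary outcome is a single contrast between two visits. The model named for it has three effects (time, group, interaction), none of them designated as the test of that contrast. With all four scheduled visits in the model, the interaction merges the primary contrast with two secondary ones, and the group main effect averages in T0, before any treatment. The model sentence has no condition term either, although condition is the stratum of randomisation and determines which active protocol is given.

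The confirmatory claim is therefore open. An effect seen only at T1 or T3 could be reported as a positive efficacy result, and a real T2 effect could be missed. It is also unsettled whether the trial's answer is one pooled result or three results by condition.

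**Working it through.** **1. The plan's sample size.** Inputs from Sample size, recruitment: δ = 7.25, σ = 7.70, power 80%, α = 5% (taken as two-sided), Lehr's formula, 90% follow-up.

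- n per arm = 16 × (7.70/7.25)² = 18.05; 18.05/0.9 = 20.05, so 20 per arm.
- 2 × 20 = 40 per condition; 3 × 40 = 120, as stated.

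The 120 is thus three separate two-arm comparisons, each with about 18 evaluable per arm. The t-test on T0-to-T2 change has noncentrality 7.25/(7.70 × √(2/18)) = 2.82 on 34 df, and power 78%.

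**2. Interaction with all four visits, one condition, 18 per arm.** Assumptions: compound symmetry, and SD of a two-visit change 7.70, so residual variance is 7.70²/2 = 29.645. With d_t the arm difference at visit t and d̄ its mean, λ = (18/2) × Σ(d_t − d̄)² / 29.645, referred to F(3, 102), critical value 2.69.

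| Arm difference at T0, T1, T2, T3 | Σ(d_t − d̄)² | λ | Interaction rejects | T2-change t-test rejects |
|---|---|---|---|---|
| 0, 0, 0, 7.25 (or 0, 7.25, 0, 0) | 39.42 | 11.97 | 82% | 5% |
| 0, 3.625, 7.25, 3.625 | 26.28 | 7.98 | 63% | 78% |
| 0, 3.625, 7.25, 0 | 36.14 | 10.97 | 79% | 78% |
| 0, 3.625, 7.25, 7.25 | 36.14 | 10.97 | 79% | 78% |
| 0, 7.25, 7.25, 7.25 | 39.42 | 11.97 | 82% | 78% |
| 0, 0, 7.25, 7.25 | 52.56 | 15.96 | 92% | 78% |

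Simulation (4,000 trials per scenario) agrees: 0.82–0.83 against 0.04–0.06 for the first row, and 0.64 against 0.79 for the second. On T0 and T2 alone the interaction is the t-test on change, with power 78%.

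**3. Group main effect, same setting.** For differences 0, 3.625, 7.25, 7.25 the mean is 4.53. The variance of a patient's four-visit mean is [29.645/(1 − r)] × (1 + 3r)/4, and λ = 4.53²/(2 × variance/18) on F(1, 34).

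- r = 0.7: variance 76.6, λ = 2.41, power 33%
- r = 0.8: variance 126.0, λ = 1.47, power 22%
- r = 0.9: variance 274.2, λ = 0.67, power 13%

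**4. Pooling the conditions, a different analysis (about 54 evaluable per arm).** If three equally spaced condition mean gains span w points, their variance is w²/6. Leaving condition out multiplies the SE by √(1 + (w²/6)/7.70²).

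- w = 4: √(1 + 2.67/59.29) = 1.02
- w = 12: √(1 + 24/59.29) = 1.19

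The SE is inflated by 2–19%. The span is an assumption. Separately, a 7.25 effect in one condition only becomes 7.25/3 = 2.42 when pooled, with power about 37%. A common 7.25 effect has power above 99%.

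**5. The non-normal branch.** The Friedman test ranks visits within each patient. It compares visits, has no arm term and takes no covariates. It cannot compare the arms, which is the task the section gives it, or carry the promised adjustment.

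**The case against.** The section does not say which visits enter the RM-ANOVA, and the outcomes are defined pairwise. On T0 and T2 alone the interaction is exactly the primary comparison. A reader might infer that the plan specifies a four-visit model which cannot test its primary outcome. The text does not support that: four visits is a reading of the schedule.

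A reader might also infer that the plan ignores condition and baseline. It does not. The section tests intervention against control within each condition, which fits the randomisation and the sample size, and it states that "baseline characteristics will be used as covariates for adjustment". That may include condition and baseline FMA-UL, and nothing rules out running the RM-ANOVA by condition.

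The power loss is not general. The interaction does as well as the T2 test, or better, for a sustained effect, and also for one that is gone by T3 after a half effect at T1. The 82% case requires a full effect at one other visit and none at T2. The 18-per-arm figures and the pooled SE inflation belong to different analyses and cannot be added together.

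All of this stands and limits the claim. An unseen SAP could list visits and covariates, but the protocol itself names the efficacy model. A two-visit reading, or a primary role for the tests by condition, has to be supplied by the reader. The Friedman branch is wrong under any reading.

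**Conclusion.** The point holds in a limited form. Statistical methods designates no primary analysis. The RM-ANOVA it names is not tied to the T0-to-T2 FMA-UL change and has no explicit condition term, while the comparison the trial was sized for is supplementary and on undefined parameters.

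How much this matters depends on the reading taken. With two visits, within condition, nothing is lost. With all four visits, a significant interaction does not establish a T2 effect (about 82% rejection with a zero T2 effect in the extreme case). Power is about 63% against 78% if the effect is half at T1 and T3, and 79–92% if it is sustained. The group main effect would be a poor primary test, at 13–33%. Pooling without condition costs 2–19% in SE for gains spanning 4–12 points.

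The within-patient correlations, compound symmetry, effect profiles and spread of condition gains are assumptions; the document gives none of them. The stronger conclusion, that the planned analysis cannot test the primary outcome or disregards condition, is not supported.

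**What to change.** - Name one primary analysis of FMA-UL at T2: ANCOVA, or the T2 contrast of a mixed model for repeated measures, with arm and baseline FMA-UL.
- Fit it within each condition, as the sample size implies, or pooled with study condition as a three-level factor, and state which of the two is primary. If by condition, say how the three results are to be read together, since three independent tests at 0.05 carry a family-wise error of 1 − 0.95³ = 14.3%.
- List the covariates in advance. Adjustment for hospital is optional.
- Report the adjusted difference with its 95% CI.
- Drop the Shapiro-Wilk switch to the Friedman test.
- Keep T1, T3 and the all-visit interaction as secondary.

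The cost is wording, provided it is settled before unblinding. FMA-UL at every visit, study condition and hospital are already collected, and the sample size does not change if the analysis within condition is primary, with each test kept at 5%.
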